**7.4.3.2 Hypotheses and Specific Data Analysis Plans**

Hypothesis 1: The IOP-PE treatment will result in larger reductions than the Massed-PE treatment in clinician-assessed PTSD symptoms on the CAPS-5 and self-reported PTSD symptoms on the PCL-5 at the posttreatment, 3-month, and 6-month follow-up points.

Hypothesis 2: The IOP-PE treatment will result in a larger percentage of participants who no longer meet clinician-assessed PTSD on the CAPS-5 than the Massed-PE treatment at the posttreatment, 3-month, and 6-month follow-up points.

Hypothesis 3: The IOP-PE treatment will result in greater improvements than the Massed-PE treatment in functional outcomes on the Sheehan Disability Scale and the Brief Inventory of Psychosocial Functioning at the posttreatment, 3-month, and 6-month follow-up points.

The analysis method for Hypotheses 1-3 will be mixed effects regression models with repeated measures. The general linear mixed model is appropriate for dimensional measures that are approximately normally distributed such as the CAPS-5 and PCL-5 (Hypothesis 1) and measures of self-reported symptoms (Hypotheses 3). For diagnosis (Hypothesis 2), the generalized linear mixed model is appropriate specifying binomial error and a logit link function. Fixed effects are treatment (Massed-PE vs. IOP-PE), time (post-treatment, 3 & 6 month FU), and the interaction of treatment by time, with baseline level used as a covariate when available. Planned contrasts will be done to test the significance of pre-post change within each treatment. The primary tests for Hypotheses 1 and 3 will be the difference between treatments in these pre-post change scores. For Hypothesis 2, it is the difference in proportion remitted post-treatment (all participants have PTSD pre-treatment). Stability of outcomes will be examined by evaluating the significance of changes after treatment and comparing baseline to the follow-up scores in each treatment condition. It is hypothesized that similar improvements will be found in service members and veterans, but the study is not powered to detect significant noninferiority differences.

**7.4.3.3 Statistical Power.** The primary hypotheses are tests of treatment differences in pre-post means using the pre-treatment score as a covariate. Statistical power for the analysis of covariance with  $r = .50$  between baseline and post-treatment is .81 to detect a standardized mean difference of .35. An analysis of unadjusted pre-post difference scores with  $N = 100$  per group would have power = .80 for a standardized difference of about  $d = .40$ . Cohen (1988) defined  $d = .2$  as "small," and  $d = .5$  as "medium." The PCL-5 in our experience has a baseline standard deviation of about 15, and smaller differences than  $d = .35$  are unlikely to be clinically meaningful. For differences in diagnostic proportions (Hypothesis 2),  $N = 100$  gives power = .80 for a difference of about 20% (i.e., 45% vs. 65% or 50% vs. 70%). This is an odds ratio of about 2.3, roughly equivalent to Cohen's  $d = .45$ . For bivariate correlations,  $N = 100$  has power = .88 to detect a medium  $r = .30$ .

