## 6. RESEARCH DESIGN

The proposed randomized controlled trial will examine the efficacy of Massed-Prolonged Exposure (Massed-PE) versus Intensive Outpatient Program Prolonged Exposure (IOP-PE) for the treatment of combat-related PTSD in active duty service members and veterans who deployed post-9/11. Both treatments are active, therapist-delivered behavioral treatments. The design of the study is summarized in Figure 1.

The *independent variable* is the treatment condition (Massed-PE or IOP-PE) to which participants are assigned. Equal randomization between both groups will occur. For Hypotheses 1 and 2, the *primary dependent variables* include self-reported PTSD symptoms on the PTSD Checklist-DSM-5 (PCL-5) and PTSD diagnosis and severity as measured by Clinician-Administered PTSD Scale for DSM-5 (CAPS-5) administered by independent evaluators blind to study condition, respectively. For Hypothesis 3, the primary dependent variables include level of disability as measured by the Sheehan Disability Scale (Sheehan, 1983; Sheehan et al., 1996) and psychosocial functioning as measured by the Brief Inventory of Psychosocial Functioning (Marx, 2011). These measures will be administered at the pre-treatment, post-treatment, 3 month follow-up and 6-month follow up assessment periods.

Participants will be asked to complete the CAP Common Data Elements battery, which includes over 25 self-report measures, including: demographics and military history; personality; deployment stress, adversity, trauma; psychiatric symptoms and history; TBI; substance use; functional impairment; sources of support; sleep impairment; pain; relationship functioning; and treatment credibility expectancy as well as blood collection to use for evaluation of possible biomarkers of PTSD, response to PTSD treatment, and psychosocial functioning. This battery will be used to measure *secondary dependent variables* (i.e., changes in psychosocial functioning including psychiatric symptoms; substance use; functional impairment; sources of support; sleep impairment; pain; and relationship functioning) as well as key moderators and mediators (i.e., military history; personality; trauma history; TBI; treatment credibility and expectancy). A list of measures is provided below in section 7.3.

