## 7. RESEARCH PLAN

### 7.1 Selection of Subjects

**7.1.1. Subject Population.** This study will consent and screen 400 active duty military personnel and veterans seeking behavioral health treatment for PTSD to randomize 250 for analysis. Both active duty and veterans will be recruited for treatment at one of four performance sites: the San Antonio Military Medical Center (SAMMC), located at Joint Base San Antonio (JBSA) - Fort Sam Houston, Texas; University of Texas Health Science Center, San Antonio, Texas; Carl. R. Darnall Army Medical Center at Fort Hood in Killeen, Texas; and Central Texas Veterans Health Care System, Doris Miller VA Medical Center, VISN 17 Center of Excellence for Research on Returning War Veterans, Waco, Texas. Enrollment will be competitive in an effort to meet the enrollment goals for the study.

**7.1.2. Source of Research Material.** All measures are being administered for research purposes. For a complete list of measures, see Section 7.3.

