***Intensive Outpatient Program Prolonged Exposure (IOP-PE)***

*The IOP-PE will include the same primary treatment components as the Massed-PE protocol plus six augmentations to maximize outcomes and target military-relevant components not previously evaluated. Similar to the Mass-PE, participants will have 3 consecutive weeks to complete treatment; however, the treatment window may be extended another week if necessary.*

1. Clinic-Based Completion of Daily Homework Assignments. Participants in the IOP-PE arm will complete all of their homework assignments in the IOP clinic, with the exception of in vivo exposure exercises. Patients will be provided with a private clinic office listen to the 90-minute PE session audiotope. Listening to audiotapes of treatments sessions, especially the imaginal exposure portion, is considered to be a key component of PE therapy. However, this component can be emotionally difficult and it is sometimes avoided. Providing structure and support to listen to the audiotope in the clinic will help ensure the completion of this PE component. Participants will be encouraged to take notes while listening to the audiotope about any portion that is impactful to them or that they would like to discuss during the brief processing session to be held with a therapist immediately after reviewing the audiotope (see below). Pilot data using this approach has demonstrated that this requires only about 15 minutes of additional therapist time with the potential to significantly improve outcomes.

2. Brief Therapist Feedback Sessions. Therapists will provide two 15-minute feedbacks sessions. The first will be after in vivo exposure homework to review any difficulties or challenges that may have occurred and to plan for the next in vivo exercise. The second will be after the listening to the PE session audiotope to focus on cognitive and emotional processing of the session.

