## 7.4 Statistical Consideration

**7.4.1 Sample Size Estimation.** The primary hypotheses are tests of treatment differences in pre-post means using the pre-treatment score as a covariate. Statistical power for the analysis of covariance with  $r = .50$  between baseline and post-treatment is .81 to detect a standardized mean difference of .35. An analysis of unadjusted pre-post difference scores with  $N = 100$  per group would have power = .80 for a standardized difference of about  $d = .40$ . Cohen (1988) defined  $d = .2$  as “small,” and  $d = .5$  as “medium.” The PCL-5 in our experience has a baseline standard deviation of about 15, and smaller differences than  $d = .35$  are unlikely to be clinically meaningful. For differences in diagnostic proportions (Hypothesis 2),  $N = 100$  gives power = .80 for a difference of about 20% (i.e., 45% vs. 65% or 50% vs. 70%). This is an odds ratio of about 2.3, roughly equivalent to Cohen’s  $d = .45$ . For bivariate correlations,  $N = 100$  has power = .88 to detect a medium  $r = .30$ .

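### Treatment is delivered by therapists who will be shared between participants, but the primary models name no therapist term and the stated power assumes independent participants

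*Protocol*

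**What the plan says.** Section 6 states that "Both treatments are active, therapist-delivered behavioral treatments". Section 7.1.8 describes 15 individual sessions of 90 minutes in Massed-PE. IOP-PE keeps those components and adds further contact: "Therapists will provide two 15-minute feedbacks sessions", and three booster sessions follow treatment. Section 7.1.1 plans "to randomize 250 for analysis" at four performance sites, and section 6 adds that "Equal randomization between both groups will occur".

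Section 7.4.3.2 chooses mixed-effects models with repeated measures for Hypotheses 1-3, linear for the scales and logit for diagnosis: "Fixed effects are treatment (Massed-PE vs. IOP-PE), time (post-treatment, 3 & 6 month FU), and the interaction of treatment by time", plus baseline where available. It does not list the random effects. Section 7.4.3.1 leaves room for site and for covariates found in baseline comparisons, and discusses active-duty or veteran status. Therapist is mentioned nowhere in 7.4.

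Sections 7.4.1 and 7.4.3.3 give the same power text. With a baseline to post-treatment correlation of .50, power "is .81 to detect a standardized mean difference of .35". Power of .80 is given for a difference of about 20 percentage points in remission. Neither section mentions an intraclass correlation (ICC) or a design effect.

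**The concern.** Participants of one therapist share that therapist's skill and style, so their outcomes are likely to be correlated. Therapist numbers and caseloads are not given. However, treating 250 people without sharing would take about 250 therapists, so some sharing is unavoidable.

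If the arms have different therapists, a difference between two small groups of therapists is confounded with the difference between IOP-PE and Massed-PE. A model that handles only repeated measures within a participant would then give standard errors that are too small for CAPS-5, PCL-5, remission and both functioning scales, and the trial's superiority claim would rest on them. If each therapist treats in both arms, therapist differences largely cancel from the comparison. The protocol does not say which arrangement applies.

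**Working it through.** **Inputs from the protocol:** d = .35, r = .50, 100 per group in the power text, 250 randomised 1:1 (125 per arm).

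**Assumptions:** two-sided 5% test (not stated; one-sided gives .887, which does not match .81); therapist ICC of .01 to .10 as a share of the baseline-adjusted variance; k = 4 to 20 therapists per arm with equal caseloads m = n/k.

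**Step 1: reproduce the stated power.**
- Adjusted SD factor: √(1 − .50²) = .866.
- Standard error: .866 × √(2/100) = .1225.
- Standardised effect: .35/.1225 = 2.858.
- Power: Φ(2.858 − 1.960) = .815, or .812 with a noncentral t on 197 df.

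This matches .81 with no variance inflation. The companion figures also fit independent participants: d = .40 unadjusted gives .807, 45% vs 65% gives .816, and 50% vs 70% gives .828. At 125 per arm the independent figure for d = .35 is .89.

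**Step 2: therapists nested in arm.**
- Design effect: DEFF = 1 + (m − 1) × ICC.
- False-positive rate when therapist is ignored: 2 × [1 − Φ(1.96/√DEFF)].
- Power of a valid test: noncentral t with 2(k − 1) df and noncentrality .35/(.866 × √(2/n) × √DEFF).

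Example with n = 100, k = 10, ICC .05: m = 10, so DEFF = 1 + 9 × .05 = 1.45. The false-positive rate is 2 × [1 − Φ(1.96/1.204)] = .104. The noncentrality is 2.858/1.204 = 2.37 on 18 df, giving power .61.

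Each cell shows false-positive rate / valid-test power:

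| n per arm | k per arm | ICC .01 | ICC .05 | ICC .10 |
|---|---|---|---|---|
| 100 | 4 | .078 / .58 | .186 / .37 | .288 / .26 |
| 100 | 5 | .072 / .63 | .160 / .44 | .250 / .32 |
| 100 | 10 | .060 / .74 | .104 / .61 | .155 / .50 |
| 100 | 20 | .055 / .78 | .074 / .72 | .098 / .65 |
| 125 | 5 | .078 / .71 | .186 / .47 | .288 / .33 |
| 125 | 10 | .063 / .82 | .118 / .67 | .181 / .54 |
| 125 | 20 | .056 / .86 | .081 / .79 | .112 / .71 |

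Simulation (20,000 replicates) agrees on the false-positive rate at 100 per arm: .160 for k = 5 and .102 for k = 10 at ICC .05.

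The power column is that of a test on therapist means. It includes the cost of few degrees of freedom: even at ICC 0 it gives .67 with 4 therapists per arm and .80 with 20. With the normal approximation, the figures at ICC .05 and 100 per arm are .53 for k = 5 and .66 for k = 10.

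**Step 3: therapists crossed with arm.** If the treatment effect is the same for every therapist, simulation of the model without a therapist term gives a false-positive rate of .038 to .050 and power of .81 to .82. Letting the treatment effect vary by therapist (variance .02) raised the rate to .057 at most. Adding a therapist term at ICC .05 moved power from .815 to .827.

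**The case against.** The strongest reply is that this is silence, not error. The quoted sentence lists fixed effects, whereas therapist would be a random effect. The protocol does not list random effects, and an SAP that is not shown may include one. That stands as a limit: the model text cannot be read as ruling a therapist term out. It does not rescue the power text, because no later document changes what .81 assumes.

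A reader might infer that the false-positive rate is well above 5% and that the stated power will not be delivered. The documents do not support that. They do not say that therapists work in one arm only, and they give no ICC, therapist number or caseload. At ICC .01 with 10 to 20 therapists per arm, the rate is 5.5% to 6% even under nesting. Section 7.4.3.1 plans to collect outcomes on everyone randomised; with 125 analysed per arm, power still reaches .82 at ICC .01 with 10 therapists per arm.

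The row with 4 therapists per arm is also an extreme. If both arms run at all four sites, it means one single-arm therapist per arm at each site throughout. Nor is site the only extra term the protocol contemplates, since other covariates are allowed for.

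**Conclusion.** The point holds in conditional form. Treatment is therapist-delivered, therapists must be shared, no therapist term is named, and the .81 and .80 figures contain no allowance for clustering.

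Under nesting with 100 analysed per arm, ignoring therapist gives a false-positive rate of about 5.5% to 29% over the assumed range (7% to 19% at ICC .05). Valid-test power is about .26 to .78 (.37 to .72 at ICC .05). Analysing 125 per arm improves power but not the false-positive rate, which rises with caseload.

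Under full crossing with a constant treatment effect there is no inflation and no loss. All of these sizes rest on ICCs and therapist numbers that the protocol does not give. The change is still worth making: a therapist term addresses the error rate in the nested case and costs nothing material in the crossed case.

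**What to change.** - In 7.4.3.2, add a random intercept for treating therapist to the linear and logit models for Hypotheses 1-3. Use small-sample degrees of freedom, such as Kenward-Roger, for the linear models.
- Record the treating therapist for each participant as a data item. The protocol describes therapist notes at one site and recordings labelled by participant ID, so this should not be left to reconstruction.
- In 7.4.1 and 7.4.3.3, state that .81 and .80 assume no therapist clustering, and say whether therapists work in one arm or both. If they are nested or partly nested, show power over a range of ICCs and caseloads.

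The cost is wording, one data field and one model term, with no extra participants. The downside is wider intervals and lower stated power if therapists are nested.

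Requiring every therapist to treat in both arms is not recommended here. It would change trial conduct, with staffing consequences and a risk of carrying IOP-PE elements into Massed-PE.

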**PRELIMINARY EVIDENCE.** Prolonged Exposure (PE) is the PTSD treatment most extensively evaluated in clinical trials with civilians and veterans, and there is strong scientific evidence to support its efficacy (Bisson, et al., 2007; Blount et al., 2013; Cigrang et al., 2005, 2011, 2015; Foa et al., 2015; Peterson, Foa et al., 2011; Peterson, Luethcke et al., 2011; Powers et al., 2010). The results of the numerous PE studies with a variety of populations led to the evaluation of PE in the largest randomized clinical trial (RCT) to date (N = 370) to evaluate the treatment of combat-related PTSD in an active duty military population. The study titled "Prolonged Exposure for PTSD among OEF/OIF Personnel: Massed vs. Spaced Trials" (PI: [name]) was funded in 2008 by the DoD as part of the STRONG STAR Consortium. The study includes four treatment arms: (1) Spaced-PE; (n = 110; ten 90-minute weekly PE sessions); (2) Present Centered Therapy (n = 110; ten 90-minute weekly PCT sessions); (3) Massed-PE (n = 110; ten 90-minute daily PE sessions on weekdays over 2 weeks); and (4) Minimal Contact Control (n = 40; weekly contact over 4 weeks to provide a posttreatment comparison group for M-PE). An analysis was conducted of the first 75 participants randomized to Massed-PE versus the 40 participants randomized to the Minimal Contact Control (Foa et al., 2015). The results indicated that reductions in interviewer-assessed PTSD severity were significantly greater in the Massed-PE group than the Minimal Contact Control, and a larger proportion of Massed-PE participants lost their PTSD diagnosis (46%) as compared to the Minimal Contact Control group (23%). Similar results were obtained in a preliminary review of the initial 1-month posttreatment outcomes of the full RCT, indicating that the outcomes of the Massed-PE and Spaced-PE groups were nearly identical. This provides the first data to date to indicate that PE delivered in a massed format (i.e., ten 90-minute PE sessions delivered on weekdays over 2 weeks) will result in similar treatment outcomes to those of PE delivered in the standard spaced format (i.e., ten 90-minute PE sessions delivered over 8 weeks).

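### Maintenance of gains is examined by within-arm significance tests with no interval or margin, and neither a significant difference from baseline nor a non-significant change after treatment can show it

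*Protocol*

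**What the plan says.** Section 7.4.3.2 sets mixed models for Hypotheses 1 to 3, with treatment, time (post-treatment, 3 and 6 months) and their interaction, and baseline as a covariate. The primary tests are between-arm: the difference in pre-post change for Hypotheses 1 and 3, and for diagnosis: "For Hypothesis 2, it is the difference in proportion remitted post-treatment (all participants have PTSD pre-treatment".

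Durability gets one sentence: "Stability of outcomes will be examined by evaluating the significance of changes after treatment and comparing baseline to the follow-up scores in each treatment condition". So there are two comparisons, both within arm: change after the end of treatment, judged by significance, and follow-up against baseline. The section gives no interval, margin or definition of a stable outcome.

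Elsewhere the protocol has a view on size. Sections 7.4.1 and 7.4.3.3 say that "smaller differences than $d = .35$ are unlikely to be clinically meaningful", with a PCL-5 standard deviation of about 15. That threshold is stated for the treatment comparison and is not carried over to stability.

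**The concern.** Stability is a claim that little has been lost since treatment ended. A significance test of change after treatment can show loss, but its failure to reach significance does not show absence of loss, and fewer follow-up data make that failure more likely. The baseline comparison uses the wrong starting point: it asks whether any improvement remains, not whether the improvement at post-treatment was kept.

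All three hypotheses name the 3- and 6-month points, and only IOP-PE has booster sessions, which Section 7.1.8 directs at keeping and extending gains. Maintenance is therefore a question on which the arms may differ by design. Two separate within-arm p-values could lead to a report that one arm held its gains and the other did not, without comparing them.

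**Working it through.** **Inputs.** n = 100 per group, r = .50, d = .35 and SD = 15 PCL-5 points (Sections 7.4.1, 7.4.3.3). 250 randomized equally, so 125 per arm (Sections 7.1.1, 6). Effect sizes of .78 to 1.10 come from Section 5, where they compare PE or CPT with control conditions; they are used here only as an assumed total within-arm gain. Loss of diagnosis of 46% with Massed-PE and 23% with Minimal Contact Control comes from Section 5, Preliminary Evidence. Assumptions: two-sided 5% (no alpha is stated), equal SDs over time, r = .50 also between later visits, and paired tests standing in for the model contrasts.

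**The plan's own figure.** The covariance analysis has SE = √(1 − .50²) × √(2/100) = .866 × .1414 = .1225 SD. Then .35/.1225 = 2.86, and power is .81, as stated. One-sided testing would give .89, so two-sided 5% is the consistent reading.

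**Baseline to follow-up, scores.** SD of change = √(2(1 − .50)) = 1 SD, so SE = 1/√100 = .10 SD. Power is from the noncentral t with noncentrality (remaining gain)/.10.

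| Share of gain lost | Remaining, from .78 SD | P(significant) | Remaining, from 1.10 SD | P(significant) |
|---|---|---|---|---|
| half | .39 | .97 | .55 | 1.00 |
| three quarters | .195 | .49 | .275 | .78 |
| 90% | .078 | .12 | .11 | .19 |
| all | 0 | .05 | 0 | .05 |

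**Baseline to follow-up, if applied to diagnosis.** Everyone starts with PTSD, so all discordant pairs go one way. Exact McNemar rejects from 6 remitters upward (2 × .5⁶ = .031; with 5 it is .0625). At 23% remitted, P(6 or more of 100) exceeds .9999. At 10% it is .94.

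**Change after treatment, scores.** Chance that a true worsening is non-significant, r = .50:

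| True worsening | n = 75 | n = 100 | n = 125 |
|---|---|---|---|
| .20 SD (3 points) | 60% | 49% | 40% |
| .25 SD (3.75 points) | 43% | 30% | 21% |
| .35 SD (5.25 points) | 15% | 7% | 3% |

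With r = .70 and n = 100 the first two miss rates fall to 28% and 11%.

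At n = 100 the 95% half-width is 1.984 × .10 = .198 SD. A just non-significant worsening therefore has an interval reaching 2 × .198 = .40 SD, about 6 PCL-5 points, beyond the protocol's own .35. At n = 125 it reaches about .35 SD; with r = .70 and n = 100, about .30 SD.

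**Change after treatment, diagnosis.** Exact McNemar, n = 100, with assumed splits of relapsed/newly remitted per 100:

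| Net loss of remission | Splits | Missed |
|---|---|---|
| 10 points | 12/2 to 20/10 | 27% to 63% |
| 20 points | 25/5 to 30/10 | 4% to 12% |
| 23 points (46% to 23%) | 25/2 to 33/10 | 0.1% to 6% |

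For the 10-point loss the range is 15% to 53% at n = 125.

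**The case against.** A reader might infer that the baseline comparison is almost certain to be significant even if all benefit is lost. For scores this is wrong: on full return to baseline it rejects at 5%. Near-certainty needs about .4 SD or more of improvement to remain, and the documents give no score-scale figure for improvement without active treatment. The 23% supports near-certainty only for diagnosis. That figure comes from a 40-person group with weekly contact, and the stability sentence speaks of scores, so a baseline test on diagnosis is not clearly planned.

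A reader might also infer that an arm falling from 46% to 23% remitted would be declared stable. It would not escape: the first comparison catches that fall 94% or more of the time at n = 100. Nor does the protocol say that a non-significant change will be called stable. That is an inference, although no other criterion is offered.

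Further, the analysis is supplementary, n = 100 already allows for 20% loss from 125, and the test is adequate for scores at the size the protocol itself calls meaningful. A .25 SD loss lies below that size. Margins and interval reporting may properly sit in the SAP, which is not shown. All of this stands and limits the point. It does not rescue the stated method: the protocol names significance and baseline comparison as its evidence on stability, and neither measures maintenance.

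**Conclusion.** The point holds in a limited form. Significance against baseline is compatible with losing half the gain (.97 to 1.00) and often with losing three quarters (.49 to .78). Non-significance after treatment is compatible with moderate loss: 49% to 30% missed for .20 to .25 SD, and 27% to 63% for a net 10 points of remission, at n = 100. Large losses would usually be detected. The primary between-arm tests are not affected; what is exposed is any statement that gains were maintained in an arm.

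The figures rest on two-sided 5%, r = .50 after treatment as well as before it, the assumed gain of .78 to 1.10 SD, and the assumed discordance. A higher correlation improves the test of change after treatment. The documents give no dropout rate, so n = 75 to 125 is a range, not a forecast.

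**What to change.** Replace the stability sentence in Section 7.4.3.2 with wording to this effect:

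- Maintenance will be assessed from the model-estimated change from post-treatment to 3 and 6 months in each arm, and from its between-arm difference, each with a 95% confidence interval.
- For diagnosis, the net change in proportion remitted, and the proportion relapsed among those remitted at post-treatment, will be reported with 95% intervals.
- A non-significant change alone will not be reported as stability.
- Change from baseline to follow-up will be descriptive only.

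If a maintenance margin is wanted, the sponsor should set and justify it in advance. The protocol's d = .35 (.35 × 15 = 5.25 PCL-5 points) is one candidate, but it was stated for the treatment comparison. With that margin, no true change and r = .50, the chance of excluding a loss of that size is Φ(.35/.10 − 1.96) = 94% at n = 100 and 97% at n = 125. Half the margin gives 42% and 50%.

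The cost is wording and a few added contrasts on the same data and model. The downside is that some arms will be reported as inconclusive rather than stable.
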